## Abstract

**Background:**

Despite the availability of a wide variety of evidence-based treatments for major depressive disorder (MDD), many patients still experience impairments in their lives after remission. Programs are needed that effectively support patients in coping with these impairments. The program Storytelling and Training to Advance Individual Recovery Skills (STAIRS) was developed to address this need and combines the use of peer contact, expert-by-experience guidance, family support and professional blended care. The aim of the planned study is (1) to assess the efficacy of the STAIRS program in patients with remitted MDD, (2) to investigate patients’ subjective experiences with STAIRS, and (3) to evaluate the program’s cost-effectiveness.

**Methods:**

A concurrent mixed-methods randomized controlled trial design will be used. Patients aged between 18 and 65 years with remitted MDD (*N* = 140) will be randomized to either a group receiving care as usual (CAU) + the STAIRS-program or a control group receiving CAU + some basic psychoeducation. Quantitative efficacy data on functional and personal recovery and associated aspects will be collected using self-report questionnaires at the start of the intervention, immediately following the intervention, and at the six-month follow-up. Insights into patients’ experiences on perceived effects and the way in which different program elements contribute to this effect, as well as the usability and acceptability of the program, will be gained by conducting qualitative interviews with patients from the experimental group, who are selected using maximum variation sampling. Finally, data on healthcare resource use, productivity loss and quality of life will be collected and analysed to assess the cost-effectiveness and cost-utility of the STAIRS-program.

**Discussion:**

Well-designed recovery-oriented programs for patients suffering from MDD are scarce. If efficacy and cost-effectiveness are demonstrated with this study and patients experience the STAIRS program as usable and acceptable, this program can be a valuable addition to CAU. The qualitative interviews may give insights into what works for whom, which can be used to promote implementation.

**Trial registration:**

This trial was registered at ClinicalTrials.gov on 1 July 2021, registration number NCT05440812.

**Supplementary Information:**

The online version contains supplementary material available at 10.1186/s12888-023-05213-w.

## Background

Major depressive disorder (MDD) is a highly prevalent and recurring disorder with a strong negative impact on patients, their family members and society as a whole [1–3]. Epidemiologic studies show that approximately 5% of the adult general world population is currently suffering from MDD, which affects approximately 280 million people, making it a leading cause of disability [4]. Treatments to effectively address the negative impact of depression are therefore highly needed.

The acute treatment of MDD symptomatology usually consists of prescription of antidepressant medication and psychological interventions, often in combination [5]. Previous research has shown that these treatments are moderately effective and that 50 to 60% of patients do not achieve an adequate response to treatment [6–9]. Importantly, of the patients, who are considered as remitted from MDD based on their symptom severity, more than half do not subjectively consider themselves to be in full remission, as they still experience functional impairments, deficits in their coping ability and lower quality of life [10]. The collective results from most treatment studies thus represent a rather narrow approach to the concept of recovery, as they have exclusively focused on evaluating treatment effects on the presence and severity of symptoms [11]. This does not necessarily align well with patients’ subjectively experienced recovery process. In fact, in their desired treatment outcome, patients place an emphasis on aspects such as finding new ways of daily functioning, feeling in control again, regaining a sense of meaning in life and the ability to undertake activities with their loved ones again, in addition to symptom reduction [12–14].

To address the aspects that are seen as important by patients themselves, two domains have been added to the concept of recovery in the past decades by community-oriented social psychiatry and the consumer movement (e.g., the antipsychiatry movement and the disability rights movement). The first domain focuses on restoring functioning after depression and is referred to as *functional recovery*. In this domain, the focus lies on enabling patients to manage tasks at work/school, engage in meaningful relationships and perform daily activities [15]. The second domain focuses on redefining a patient’s identity and is referred to as *personal recovery*. A widely used definition of personal recovery is that of Anthony [16], describing it as a unique and personal process in which patients find a new balance in life where they are satisfied, hopeful and feel they have a meaningful life, even when there remain limitations caused by an illness. The key aspect of personal recovery is the ability of patients to find a new identity, in which they feel in control again and have hope for the future. Both functional and personal recovery relate to patients’ well-being and are therefore included in a broader view on recovery, which has been adopted in MDD treatment guidelines [5]. This broader view on recovery fits in with the shift in mental healthcare towards an approach in which the patient perspective is given more attention and health is seen as more than the absence of physical, mental and social obstacles [17].

The three domains of recovery (clinical, functional and personal) complement each other but do not necessarily develop simultaneously during the recovery process [18–21]. Being in symptomatic or clinical remission does not inherently mean that someone has found a new balance in life in which they can cope with the difficulties resulting from the illness. Functional and personal recovery can lag behind clinical recovery by up to several years [22–24]. One reason for this is a stronger feeling of incompetence caused by identifying oneself with the mental illness (illness identity), which has an impact on hope and self-esteem and in turn can negatively influence coping with daily tasks, social interaction and vocational outcomes [25]. Lasting effects in the functional and personal domains are known risk factors for symptomatic relapse [15, 26]. Consequently, interventions aimed at enhancing personal and functional recovery may also contribute to perpetuating clinical recovery and preventing relapse into new depressive episodes.

The above shows that we should ideally pay more attention to personal and functional recovery in depression treatment to optimise treatment outcome in MDD patients. However, current treatment guidelines are predominantly based on efficacy studies in which outcome is defined as clinical recovery [11, 27]. One barrier to adopting a broader approach to recovery in depression treatment may be that comprehensive and well-documented programs focused on functional and personal recovery in MDD patients are currently lacking. Recovery-oriented treatments have their origin in the field of schizophrenia treatment, where complete symptomatic recovery is rare due to the chronic nature of mental problems. Therefore, to enable patients to live with their symptoms and reach or maintain an acceptable quality of life, treatment is often focused on patients’ identity and on helping patients optimize their situation in other domains (e.g., social relations, work) [28]. To the best of our knowledge, such an approach has not yet been adopted in depression treatment. As many patients suffering from MDD also experience residual symptoms after remission [29] and a long-lasting impact of the illness on their identity and daily and social functioning (e.g., managing tasks at work/school and engaging in meaningful relationships) [30], recovery-oriented treatment could also be valuable for them. This type of treatment is the focus of this study.

For treatment to promote personal recovery in mental health, Leamy et al. [31] proposed a conceptual framework, in which five recovery processes are described: (1) *connectedness* with others, (2) *hope* that there are possibilities to get better, (3) a redefined *identity* wherein there is balance between vulnerabilities and possibilities, (4) *meaning* to life (including the ability to fulfil significant roles in life) and (5) a sense of *empowerment*. These processes fit well with the nine elements of functional and personal recovery described in an earlier publication by Davidson et al. [32]: (1) renewing hope and commitment, (2) redefining self, (3) incorporating illness, (4) being involved in meaningful activities, (5) overcoming stigma, (6) assuming control, (7) becoming empowered and exercising citizenship, (8) managing symptoms and (9) being supported by others [32]. Taken together, the aspects described by Leamy et al. [31] and Davidsons et al. [32] are widely used in recovery-oriented research and form the theoretical basis for the current work. Here, the assumption is that the stronger a treatment influences these aspects, the more likely it is to contribute to functional and personal recovery. Previous research has found several elements that can be incorporated into treatment and that support one or more of these aspects. *Peer contact* has been found to promote social contact, mutual understanding, trust and self-reliance [33–35]. G*uidance by an expert by experience* has been found to raise empowerment and a feeling of hope, to improve social functioning, and to reduce stigma and self-stigma [36–38]. *Family support* has been shown to promote hope and a more positive sense of self [39, 40] and to function as a buffer against stressful life events [41]. In addition, the use of online facilities next to face-to-face contact (*blended care*) has been shown to enhance self-management, autonomy and connectedness [42–44]. To the best of our knowledge, no program that combines all of these elements to support recovery in MDD patients has previously been developed.

To address this gap, the training program ‘Storytelling and Training to Advance Individual Recovery Skills’ (STAIRS) [45] was developed by a project team (consisting of clinical professionals and experts by experience). In the STAIRS program, all of the above-described elements are integrated. Furthermore, the program is designed to foster the mechanisms that were concluded to be supportive of recovery in a recent systematic review [46]: (1) provision of information and teaching skills, (2) promotion of a working alliance, (3) the use of role modelling and (4) increasing choice and opportunities. To evaluate the STAIRS program’s efficacy in improving recovery, we aim to conduct a randomized controlled superiority trial (RCT) among MDD patients, who are in symptomatic remission. The intervention group will receive STAIRS training on top of care as usual (CAU). The comparison group will receive CAU and basic written psychoeducation about the recovery process. The primary quantitative outcome of the RCT is a measure of functional and personal recovery. Secondary outcomes include measures of depressive symptom severity, experienced control over life and cost-effectiveness. In exploratory quantitative analyses, potential demographic moderators of responding to the STAIRS-training will be investigated. Our primary hypothesis is that patients assigned to the STAIRS group will reach a significantly higher level of functional and personal recovery than the patients assigned to the comparison group. In addition, we hypothesize that the STAIRS group will show: (1) lower symptom severity and relapse rates in the first six months following the intervention, (2) lower levels of depression-related functional disabilities, (3) higher levels of perceived empowerment, (4) higher levels of perceived control of events and ongoing situations, (5) higher levels of perceived self-management skills, and (6) lower costs per quality-adjusted life year (QALY) compared to the comparison condition.

## Methods/design

### Study design

We will use a concurrent mixed methods randomized controlled superiority trial [47], comparing the STAIRS-program to CAU (with some psychoeducation) on a range of quantitative outcomes. Additionally, a qualitative study will be conducted with a subgroup of the study sample to gain more insight into the mechanisms underlying the quantitative study outcomes. Combining both types of data makes it possible to better interpret what contributes in which way for whom. This is particularly important since the intervention under study consists of a combination of aspects that interact with each other [48]. See Fig. 1 for an illustration of the design.

**Fig. 1 Fig1:**
[figure not shown]
CONSORT flowchart of the study; CAU = care as usual; PE = psychoeducation

The SPIRIT checklist is presented as an additional file and describes where the items described in the SPIRIT reporting guidelines [49] are located in this protocol. After drawing up the first protocol (approved by the Medical Ethical Committee; METc, on 21–12-2021), three amendments have been made and submitted to the METc. Amendment no. 1 (21–2-2022) concerned an adjustment in the control condition. The previous control condition deviated too much from CAU and was insufficiently in line with the phase of recovery in which the target group for this study is located. Amendment no. 2 (30–1-2023) concerned an adjustment to the inclusion criterion aimed at the phase of the treatment, in order to better align with this treatment and achieve more inclusions. A demarcation in time (i.e. the last six months of treatment) turned out to be insufficiently in line with how depression treatment proceeds in practice and has therefore been changed to a demarcation in terms of reduction of depression symptoms (i.e. a decrease in symptom severity to moderate or less). The last amendment (22–6-2023) concerned the addition of the possibility to also offer the STAIRS training online so that patients for whom physical meetings are not possible can still participate.

### Recruitment and randomization

Participants are recruited from October 2022 to June 2024 from several mental healthcare organizations in the North of the Netherlands (including the University Center of Psychiatry [UCP] from the University Medical Center Groningen [UMCG], Mental Health Services Drenthe [GGZ-Drenthe], and Dimence).

Patients can be included in the study if they are between 18 and 65 years old, receive treatment for MDD and have depressive symptom severity levels that have decreased to moderate or less, according to the Inventory of Depressive Symptomatology self-report (IDS-SR). Exclusion criteria are: a primary diagnosis of bipolar depression or depression with psychotic features, comorbid schizophrenia spectrum or other psychotic disorder, comorbid moderate or severe dependence on alcohol or drugs, and neurological disorders (e.g., dementia). Additionally, patients with insufficient command of the Dutch language, cognitive problems or indication of low IQ (i.e., < 80), who do not possess a computer or smartphone, and/or who have been referred to a different mental health service for other mental problems are excluded.

In the participating centres, treating clinicians will inform eligible patients about the study and provide contact information to the coordinating researcher (DW) when a patient is willing to participate. Also, information about this study will be shared on different social media platforms, allowing interested participants to contact the coordinating researcher themselves. Once a patient has expressed their interest in participating, a researcher will contact them to further explain the study and check eligibility. An information letter will be sent, and a patient will have a week to contemplate, after which they will be contacted again. When a patient is willing to participate, a meeting will be planned with a researcher to discuss any further questions and to sign an informed consent form.

After informed consent is obtained, patients will be randomly allocated to one of the study arms. Randomization will be performed at the patient level by a research assistant who is not involved in the study, using simple randomization with a 1:1 allocation ratio. A list with 140 randomly generated numbers (0 or 1) will be used to allocate patients in order of the date and time of the informed consent meeting. Patients who are randomized to the active intervention condition will be placed on a waiting list for the treatment in (a) the organization where they received all their previous treatment (for patients referred from organizations that offer the STAIRS training) or (b) in the UCP (for patients who are referred from organizations that do not offer the STAIRS training). The STAIRS training starts when at least three patients have been added to the waiting list. At that time, patients will receive an email inviting them to join the training. This email will contain all needed information about the date and location of the meetings and how to access the private online environment that is used as part of the STAIRS-program. When attending physical meetings turns out to be difficult for participants in the intervention condition, they will be given the option to follow the STAIRS training online. Previous pilot work showed this to be a usable and acceptable option [45].

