#### Depression-related items

*Depressive symptom severity* will be assessed using the Inventory of Depressive Symptomatology Self Report (IDS-SR) [53], which is a 30-item self-report questionnaire (of which 28 items are scored). Each item focuses on one specific aspect of symptomatology in the last week and is scored on a 4-point Likert scale (0 = no change/difficulties, 3 = strong change/difficulties). The sum score of 28 items (range 0–84) will be used, with higher scores indicating higher levels of depressive symptomatology. The IDS-SR has been shown to have high internal consistency (Cronbach’s alpha is 0.92) [54].

*Depression-related functional impairment* describes the level of impairment patients can experience due to the presence of a mental illness. This will be assessed using the 5-item self-report Sheehan Disability Scale (SDS) [55]. Three out of the five items focus on the level of impairment patients experienced in the past week with regard to their work/school activities, family relationships, and social functioning and are rated on a 10-point Likert scale. The sum score of three items (range 0–30) will be used, with higher scores indicating more disability and impairment due to depressive symptoms.

*Relapse* will be assessed at T2 to determine if a patient has relapsed in the period following treatment. Assessment will be performed by a trained interviewer using the ‘Major Depressive Episode’ (MDE) section of the Dutch version of the Mini International Neuropsychiatric Interview – Simplified (MINI-S) [56], which is a short structured diagnostic interview. The time frame will be adapted to enable assessment of relapse between T1 and T2.

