### Data analysis

#### Quantitative analyses

Before the start of the analyses, any missing values will be imputed 20 times using a fully conditional specification [74]. After multiple imputation, all analyses will be conducted in each of the 20 datasets and pooled across imputed datasets [75]. No subjects will be excluded in any phase of the data preprocessing and analyses. All analyses will be conducted according to the intention-to-treat (ITT) principle, and findings will be reported following the Consolidation of the Standards of Reporting Trials (CONSORT) guidelines [76].

The primary outcome in this study is the change in the level of subjective experienced recovery during the intervention period (T0 to T1) and at the six-month follow-up (T0 to T2). The efficacy of the STAIRS-training will be examined by comparing the change in recovery scores between the intervention group and the control group using linear regression models with the treatment group (0 = control; 1 = intervention) as the main independent variable. In subsequent analyses, subgroup differences in the change in the primary outcome will be explored by testing the interaction effects of treatment condition with a range of baseline covariates: age, gender, marital status, employment status, level of education, family composition, number of previous depressive episodes, duration of current depression, first age of onset, and sleeping problems. Intervention effects on the continuous secondary outcomes are analysed using the same approach as for the primary outcome. To investigate the effect of treatment on the relapse rate (during follow-up; T1 to T2), logistic regression will be used with relapse at T2 (1 = yes; 0 = no) as the outcome and the treatment group as the independent variable.

For all estimated linear regression models, assumptions of conditional normality, linearity and homoscedasticity will be checked by inspection of Q‒Q plots and residual plots. In case of assumption violations, outcome variables will be transformed (e.g., natural logarithm) and models rerun. If necessary, different transformations will be applied until the model assumptions are met. Imputation and statistical analyses will be conducted with SPSS and/or R. A two-sided alpha level of 0.05 will be used.

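### The sample is called remitted, but eligibility admits up to moderate symptoms, so a persisting episode can be scored as a relapse

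*Protocol article*

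**What the plan says.** **Population as described.** The Abstract (Methods) enrols "Patients aged between 18 and 65 years with remitted MDD", and its stated aim uses the same term. The Background announces a trial "among MDD patients, who are in symptomatic remission".

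**Population as enrolled.** Under Recruitment and randomization, patients must "receive treatment for MDD" and "have depressive symptom severity levels that have decreased to moderate or less", according to the IDS-SR. No remission threshold is given, and a current depressive episode is not an exclusion. The Study design section explains the origin: the second amendment replaced a limit in time by "a decrease in symptom severity to moderate or less". The criterion is current text, and so are the descriptions of remitted patients.

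**Relapse outcome.** Under Depression-related items, a trained interviewer applies the MINI-S depressive-episode section at T2: "The time frame will be adapted to enable assessment of relapse between T1 and T2". No diagnostic interview is described at T0 or T1.

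**Relapse analysis.** Under Quantitative analyses, "logistic regression will be used with relapse at T2 (1 = yes; 0 = no) as the outcome" and treatment group as the independent variable. The same section says that no subject is left out at any stage.

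**The concern.** Relapse presupposes remission. If some patients are still in an episode when the T1 to T2 window opens, a yes on the depressive-episode section can mean that the old episode continued or that a new one began. The article gives no rule for telling these apart.

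Two statements depend on the distinction. The Background hypothesises lower relapse rates with STAIRS in the six months after the programme. The Discussion would use a lower probability of relapse to argue for adding recovery-oriented programmes to symptom-focused treatment. Neither can be read as intended if the event mixes persistence with relapse. Separately, any result of the trial, including the primary one, would be reported for remitted MDD when the enrolled group is wider.

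**Working it through.** **The plan's own figures.** No rate, power or sample size is given for relapse. The stated sample size concerns a standardised difference of 0.5 and reproduces: 2 × ((1.96 + 0.84)/0.5)² = 62.7, so 63 per group, 126 in total, and 126/0.9 = 140. It does not bear on this point.

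**Step 1: passages side by side.**

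| Question | Article's answer |
|---|---|
| Must the patient be remitted at entry? | Yes by description (Abstract, Background); no by criterion (Recruitment and randomization) |
| Is a current episode established or excluded at T0 or T1? | No diagnostic interview is described |
| What is scored? | Depressive episode within T1 to T2, asked once at T2 |
| Who is analysed? | All randomised patients |
| Is a continuing episode handled differently from a new one? | Not stated |

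The list of baseline moderators under Quantitative analyses includes the duration of the current depression, which fits a sample in which some episodes are ongoing.

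**Step 2: size, as an illustration.** All rates here are assumed; the article gives none. Let u be the share of each arm with a persisting episode that is scored as relapse, and p the true relapse rate in the rest. Then:

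counted rate = u + (1 − u) × p

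odds ratio = [STAIRS rate/(1 − STAIRS rate)] / [control rate/(1 − control rate)]

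With p = 20% in control and 10% in STAIRS:

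| u | Control | STAIRS | Odds ratio | Persisting share of control events (u / control rate) |
|---|---|---|---|---|
| 0 | 20% | 10% | (0.10/0.90)/(0.20/0.80) = 0.44 | 0% |
| 10% | 0.10 + 0.90 × 0.20 = 28% | 0.10 + 0.90 × 0.10 = 19% | (0.19/0.81)/(0.28/0.72) = 0.60 | 36% |
| 20% | 0.20 + 0.80 × 0.20 = 36% | 0.20 + 0.80 × 0.10 = 28% | (0.28/0.72)/(0.36/0.64) = 0.69 | 56% |
| 30% | 0.30 + 0.70 × 0.20 = 44% | 0.30 + 0.70 × 0.10 = 37% | (0.37/0.63)/(0.44/0.56) = 0.75 | 68% |

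With 30% v 15%, the odds ratio goes from 0.41 to 0.52, 0.60 and 0.65 at the same values of u.

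**Step 3: if treatment affects persistence.** Suppose relapse is 20% in both arms, so STAIRS does nothing to relapse, but persistence is 20% in control and 10% in STAIRS. Counted rates are 0.20 + 0.80 × 0.20 = 36% and 0.10 + 0.90 × 0.20 = 28%. These are the same rates as in the 20% row above, where relapse was halved. The outcome as described cannot tell the two situations apart.

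**The case against.** The strongest reply is that the article does not say continuing episodes are coded as relapses. A moderate IDS-SR score is a self-report sum and not a diagnosis of a current episode. Patients stay in treatment, and an eight-week programme lies between T0 and T1, so some will remit before the window opens. The interviewer is trained, and the adapted interview may ask about onset, a detail that a condensed article can leave to the full protocol. This stands to a degree: a reader might infer that persisting episodes will be counted, but the text supports only that they can be, with nothing described to prevent it. The contradiction over who is enrolled is untouched by this reply.

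A reader might infer further faults that the article does not bear out:

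- **The T1 to T2 window.** An episode that starts and ends between T0 and T1 is not captured, but the hypothesis concerns the six months after the programme, and the Background, Measurements, Depression-related items and Quantitative analyses sections agree on that. It is a deliberate choice. Opening the window at T0 would count every episode still present at entry, including those that end before T1. The persisting share could only stay the same or rise; in the table above, a rise from 20% to 30% moves the odds ratio from 0.69 to 0.75.
- **No baseline-severity term.** An unadjusted comparison of randomised arms is valid, the covariate set may be left to an analysis plan that is not shown, and adjustment would not separate persistence from relapse.
- **Bias always towards no effect.** That requires persistence to be unaffected by treatment. Lower symptom severity is itself a hypothesised effect of STAIRS, so this cannot be taken for granted.

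**Conclusion.** The point holds in limited form. The article contradicts itself on whether the patients are remitted. It also defines relapse in a way that lets a persisting episode count as one, so the secondary relapse hypothesis would be tested on a mixed event.

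The size is unknown, because the article gives neither the share of unremitted patients nor any relapse rate. Under the assumed 20% v 10%, with 10% to 30% persisting equally in both arms, the odds ratio moves from 0.44 to between about 0.60 and 0.75. That dilution rests on equal persistence; otherwise the direction is open.

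A reader might infer that the whole trial is compromised. It is not: relapse is one secondary outcome, and the I.ROC comparison between randomised arms remains valid in the patients enrolled. What needs correcting there is the name of the population. The matter should be settled before analysis.

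**What to change.** 1. Reconcile the Abstract and Background with the criterion under Recruitment and randomization. If the criterion stands as written, describe the sample throughout as patients in treatment for MDD whose symptoms have fallen to moderate or less.
2. Keep the T1 to T2 window and the analysis of all randomised patients, and name that outcome major depressive episode between T1 and T2.
3. Report relapse only as an analysis in patients below an IDS-SR remission cut-off at baseline (T0), prespecified before the data are examined. The score is already collected. Because it precedes the programme, it avoids selecting patients on remission at T1, which the programme could have influenced. One detail to settle: the article places T0 in the week before the programme and allocation directly after consent, so T0 can follow allocation and a wait for a group to fill. If the IDS-SR score used to check eligibility is recorded, it is the strictly pre-randomisation alternative.

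The cost is protocol and analysis-plan wording, with no new data collection. The relapse analysis becomes smaller and less precise, and a baseline cut-off does not guarantee remission at T1, so some persisting or returning symptoms before the window can still enter.
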